The patient-reported satisfaction and quality of life after PBR have been analyzed by several authors; however, only 3 studies have evaluated them prospectively [17–19]. The main limitations of these studies are the lack of differentiation in the results between patients with breast cancer and RRM, the scarce follow-up and the absence of a preoperative assessment in one of the studies [19]. Most of the women with breast reconstruction experienced changes and deterioration of their breast during the follow-up. There are no available prospective studies that have analyzed these changes during the follow-up for RBP or PBR. Some retrospective studies detect a very low incidence of complications, cosmetic deterioration and replacement of implants [20, 21]. In contrast, prospective studies have detected a higher rate of cosmetic sequelae after PBR [18, 19]. These studies highlighted the low breast satisfaction of patients with rippling, especially those who underwent a prepectoral procedure.

Although at this time SSM/NSM with PBR constitutes a necessary surgical procedure in the oncologic setting and in the context of high risk, there is a lack of prospective studies that have evaluated their oncologic safety and patient-reported quality of life. Therefore, the objective of this study will be to assess prospectively and with long-term follow-up the safety of sparing mastectomies with PBR. To do this, we will analyze the safety of the technique in terms of implant loss, polyurethane safety, and surgical complications; oncological safety in terms of RGT, local relapses and new tumors; and the resilience of the reconstruction, assessing cosmetic deterioration, the need for new surgeries and long-term patient satisfaction.

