### Outcomes

Primary outcome measures.

Incidence of implant loss (Feasibility of reconstruction). To evaluate the feasibility of prepectoral reconstruction in terms of implant loss the first year after surgery, also during oncological treatment (example: chemotherapy) (Unit of mesure: number of implant loss). Implant loss is defined as the need to remove the prosthesis for any cause such as strusion, infection or necrosis.

Secondary outcome measures.

Incidence of surgical complications—reoperations (Safety). To determine the global incidence of surgical complications, as well as the causes of complications in terms of: postoperative bleeding, skin necrosis, necrosis of the nipple areola complex, seroma and infection.

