### Sample size

According to the meta-analysis by Wagner et al. [1] and the iBRA study [21], the incidence rate of implant loss is 3.3% and 9%, respectively. Our study will therefore assume that a 5% loss of implants would be acceptable and will use this value for calculating the sample size. Therefore, with a 95% confidence level (95% CI), an accuracy of 5% and assuming a 10% of potential losses during follow-up, we estimated that the necessary sample size will be 81 patients.

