### Statistical analysis

We will conduct a descriptive analysis of the variables included in the study. All quantitative variables will be expressed with the mean, standard deviation and corresponding 95% confidence interval. Comparison of proportions: The differences between the various qualitative variables will be found using Fisher’s exact test or the chi-squared test (χ2). The qualitative variables will be expressed in proportions and respective confidence intervals. The differences between the quantitative variables will be analyzed using Student’s t-test for independent groups. If the conditions of the t-test are not verified, we will use the Mann-Whitney U test. We will use Kaplan-Meier curves and compare them using the log-rank test to determine those variables related to locoregional relapse and the incidence rate of new tumors, as well as to assess cosmetic deterioration. The statistical analysis will be performed using version 24 of the statistical program IBM SPSS and Epidat 4.1.

Patients with missing data will be exclude for the analysis.

The analysis of the safety of the surgical technique will be performed on the entire sample. Oncological safety and satisfaction assessment will be analyzed by groups: oncological patients and patients with a RRM.

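### The Kaplan-Meier analysis of cosmetic deterioration makes no provision for implant loss, which ends the reconstruction being graded (secondary outcome, modest effect)

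*Protocol article*

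**What the plan says.** All references are to the protocol article.

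- **Statistical analysis** names the time-to-event method: "We will use Kaplan-Meier curves and compare them using the log-rank test to determine those variables related to locoregional relapse". The same sentence extends it to "the incidence rate of new tumors, as well as to assess cosmetic deterioration". No competing event is named, and nothing says how implant loss is coded in the cosmetic analysis. The section also provides for proportions with confidence intervals for qualitative variables.
- **Outcomes** makes implant loss in the first year the primary outcome: "Implant loss is defined as the need to remove the prosthesis for any cause such as strusion, infection or necrosis". Cosmetic sequelae are a secondary outcome, graded by the breast surgeon on Clough types I to III. Implant loss is not among those types.
- **Sample size** cites two sources in which "the incidence rate of implant loss is 3.3% and 9%, respectively", and continues: "Our study will therefore assume that a 5% loss of implants would be acceptable".
- **Study objectives** lists, as secondary aims, evaluating cosmetic sequelae after prepectoral reconstruction and identifying factors related to them.
- **Images** schedules postoperative photographs at 12–18 months and at 5 years. The **Discussion** expects most sequelae within the first 2 years.

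**The concern.** Implant loss is an early event that the design expects, and it removes the object of the cosmetic assessment. Kaplan-Meier codes each woman as having the event or as censored. Implant loss is not a listed cosmetic event, so the natural coding is to censor these women or to leave them out.

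Censoring treats a woman without an implant as if her later risk of deterioration matched that of women who kept theirs. The curve then no longer gives the share of operated women who deteriorate with the implant in place. It also leaves out the women whose reconstruction failed outright, which a patient or surgeon would hardly count as a good cosmetic result.

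For the risk-factor objective, a log-rank test with loss censored compares only the rate of deterioration among women who still have the implant. A factor that does harm partly by causing implant loss would show only part of that harm. The problem would remain with complete data and exact event dates, so it is separate from the rule that excludes patients with missing data.

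**Working it through.** **The plan's own figure.** With p = 0.05, precision d = 0.05 and 95% confidence:

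n = 1.96² × 0.05 × 0.95 / 0.05² = 72.99, so 73.

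Allowing for 10% losses: 72.99 / 0.90 = 81.1, or 73 × 1.10 = 80.3, rounded up to 81. The stated 81 reproduces, and 73 is the number evaluable.

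**Women affected.** 81 × 0.033 = 2.7; 81 × 0.05 = 4.1; 81 × 0.09 = 7.3.

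**Inputs.**
- Implant loss L: 3.3%, 5% and 9%, from Sample size.
- Loss falls in year 1, from Outcomes.
- Deterioration risk C, as one minus Kaplan-Meier at 5 years with loss censored: not given. Assumed 30% to 70%. The upper part leans on the Background remark "Most of the women with breast reconstruction experienced changes and deterioration of their breast during the follow-up", which concerns breast reconstruction in general and is not a Clough rate.

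**Case A: deterioration first gradable at 12 months, after the loss window.**
- Cumulative incidence with the implant in place = (1 − L) × C, so the overstatement is L × C.
- Deterioration or loss = L + (1 − L) × C, so the understatement is L × (1 − C).
- Standard error = √(C(1 − C)/73): 5.4 points at C = 30% or 70%, 5.9 at 50%, 5.7 at 60%.

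| Loss L | C | Overstatement, points (in SE) | Understatement of deterioration or loss, points |
|---|---|---|---|
| 3.3% | 30% | 1.0 (0.18) | 2.3 |
| 3.3% | 70% | 2.3 (0.43) | 1.0 |
| 5% | 30% | 1.5 (0.28) | 3.5 |
| 5% | 50% | 2.5 (0.43) | 2.5 |
| 5% | 60% | 3.0 (0.52) | 2.0 |
| 5% | 70% | 3.5 (0.65) | 1.5 |
| 9% | 30% | 2.7 (0.50) | 6.3 |
| 9% | 50% | 4.5 (0.77) | 4.5 |
| 9% | 60% | 5.4 (0.94) | 3.6 |
| 9% | 70% | 6.3 (1.17) | 2.7 |

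**Case B: deterioration can occur from the day of surgery.** Let λ = −ln(1 − C)/w be a constant deterioration hazard over w years, and μ = −ln(1 − L) the loss hazard in year 1. Then

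cumulative incidence = [λ/(λ+μ)] × (1 − e^−(λ+μ)) + e^−(λ+μ) × (1 − e^−λ(w−1)).

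For C = 30%, L = 5%, w = 5: λ = 0.0713, μ = 0.0513, and the cumulative incidence is 0.067 + 0.220 = 28.7%, an overstatement of 1.3 points. With w = 2 it is 28.9%, or 1.1 points. At C = 50% and w = 5 the overstatement is 1.4, 2.2 and 3.9 points for 3.3%, 5% and 9% loss.

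**Log-rank test.** Simulated with 81 women, two groups of about equal size, equal deterioration hazards (30% at 5 years), loss censored and 10,000 runs. The rejection rate at the 5% level is 4.9% (loss 5% v 5%), 4.8% (3.3% v 9%) and 5.0% (2% v 20%), so the test keeps its size.

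Power was simulated with 73 women, 40% baseline deterioration, a hazard ratio of 1.8 and loss of 3.3% v 9%. It is 41% with loss censored and 50% with loss counted as an event. If a shared frailty of variance 1 links loss and deterioration, the figures are 21% and 29%. When loss does not differ between the groups, the composite gains nothing.

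**The case against.** The strongest reply is that the article nowhere says women with implant loss are censored. Event coding often goes to an analysis plan, which is not shown here, and Kaplan-Meier works unchanged if loss is counted as an event. This stands in part. The point is therefore conditional: the article fixes the method and leaves open a coding choice whose natural default gives the wrong quantity.

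Several stronger readings are tempting, and the document does not support them:

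- *Deterioration is impossible after implant loss.* The Clough grading includes asymmetry and deformity, and the data collection list records both for all patients. Either could be graded after removal. What ends is the reconstruction named in the objective.
- *Kaplan-Meier is the only method for this outcome.* Proportions with confidence intervals are also provided for, so an all-patient figure is available.
- *The risk-factor tests are wrong, or biased toward no effect.* The log-rank test with loss censored is a valid cause-specific comparison and keeps its size. Attenuation needs a risk shared by loss and deterioration, which is plausible but not documented.
- *The plan itself expects 5–9% loss.* It assumes 5%; the cited rates are 3.3% and 9%.

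It is also fair to say that in Case A one minus Kaplan-Meier is exactly the deterioration risk among women who still have the implant at 12 months. That is a legitimate quantity if it is labelled so. Finally, testing factors only on the composite would blend the primary outcome into a separate objective, so the composite belongs in a supporting role.

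**Conclusion.** The point holds as a gap in how the cosmetic analysis is fixed. Kaplan-Meier and log-rank are assigned without providing for an expected early event that ends the reconstruction.

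If affected women are censored, the curve overstates deterioration with the implant in place by about 1 to 3.5 points at the assumed 5% loss. That is under 0.7 standard errors. The extreme is about 6 points, at 9% loss and 70% deterioration. The share with deterioration or loss is understated, by 3.5 points at 5% loss and 30% deterioration.

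These sizes rest on assumed deterioration rates of 30–70%, on loss confined to year 1, and on censoring as the coding. Log-rank results stay valid as cause-specific comparisons, but they are silent on harm through implant loss. The outcome is secondary and the effect modest, so priority is low.

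**What to change.** Add to Statistical analysis:

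> Implant loss will not be treated as ordinary censoring in the cosmetic analysis. Deterioration with the implant in place will be reported as a cumulative incidence with implant loss and death as competing events, alongside the proportion with deterioration or implant loss. Log-rank results will be described as cause-specific comparisons, with the composite event as a supporting analysis.

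No new data are needed, since implant loss is already collected as the primary outcome. The costs are a composite rate that looks slightly less favourable and possibly software other than SPSS 24 for the cumulative incidence. Settling the rule now also prevents the coding from being chosen once results are known.

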### Monitoring

The monitoring committee is made up of medical and radiation oncologists, pathologists, breast surgeons, and radiologists. This committee evaluates the inclusion of each patient in the study. Surgical complications are assessed by the unit’s surgical committee.

### Harms

In our study an adverse event will be defined as any untoward medical occurrence in a subject without regard to the possibility of a causal relationship. Adverse events will be collected after the subject has provided consent and enrolled in the study.

### Ethics and dissemination

The study has been approved by our hospital’s research ethics committee (Ethics Committee of A Coruña-Ferrol. Spain. Prospectively registered on 20/Jul/2020. Registration code: 2020/95). All included patients will sign a specific informed consent form for the study. This consent form will be delivered by the surgeon in the preoperative consultation during which the patient may ask questions. It is estimated that the preliminary data will be published 2–3 years after the study has begun and that the final data will be divulged at 6–7 years. The data obtained during this study will be published in indexed journals.

### Consent or assent

Consent will be given to the patient during the second consultation with the surgical specialist. In this consultation the intervention and the possibilities of participating in the study will be explained. in the same way, the doubts that the patient may have will be clarified. Later, the patient will talk with the nurse case manager, who will also explain the surgical technique and the results.

After this consultation, if the patient decides to participate in the study, she will sign the informed consent.

The patients are free to leave the study at any time, for this they will only have to request the consent of revocation.

### Confidentiality

All study-related information will be stored securely at the study site. All participant information will be stored in locked file cabinets in areas with limited access. All laboratory specimens, reports, data collection, process, and administrative forms will be identified by a coded ID [*identification*] number only to maintain participant confidentiality. All records that contain names or other personal identifiers, such as locator forms and informed consent forms, will be stored separately from study records identified by code number. All local databases will be secured with password-protected access systems. Forms, lists, logbooks, appointment books, and any other listings that link participant ID numbers to other identifying information will be stored in a separate, locked file in an area with limited access.

### Ancillary and post-trial care

The patients will continue to be followed up in the breast unit and the optimal treatment indicated at all times will be provided.

### Trial results

The first results will be published 3 months after including the last patient in the study, so we can assess the main result.

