### Study objectives

#### Main objective

To evaluate the safety of prepectoral reconstruction in terms of postsurgical complications and the feasibility of reconstruction (implant loss).

Secondary objectives:

To evaluate the safety of sparing mastectomy through the identification of RGT, primary carcinomas and breast cancer relapses (patients operated on for breast cancer).To assess satisfaction and quality of life after prepectoral reconstruction in women with breast cancer and those with high risk.To identify factors related to satisfaction and quality of life after prepectoral reconstruction.To evaluate the cosmetic sequelae after prepectoral reconstruction in women with breast cancer and with high risk.To identify factors related to the cosmetic sequelae after prepectoral reconstruction.

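### The main result is to be reported 3 months after the last inclusion, although the primary outcome, implant loss, runs for a full year after surgery

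*Protocol article*

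**What the plan says.** Under Outcomes, the protocol article names one primary outcome, with this aim: "To evaluate the feasibility of prepectoral reconstruction in terms of implant loss the first year after surgery, also during oncological treatment". The event is broad: "Implant loss is defined as the need to remove the prosthesis for any cause such as strusion, infection or necrosis". Surgical complications are listed separately, among the secondary outcomes.

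Under Trial results, the timing of the first report is fixed and justified by the main result: "The first results will be published 3 months after including the last patient in the study, so we can assess the main result".

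Under Ethics and dissemination, the estimate is that "the preliminary data will be published 2–3 years after the study has begun", with final data at 6–7 years. The Discussion adds that oncological safety needs at least 5 years of follow-up. No accrual period is stated.

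Under Statistical analysis, Kaplan-Meier curves are named for relapse, new tumors and cosmetic deterioration, but not for implant loss. Patients with missing data are excluded.

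**The concern.** Three months after the last inclusion, the last woman has at most 3 months of follow-up. She has less if inclusion precedes surgery, as the column order in Table 1 suggests. Everyone operated on in the closing 9 months of accrual still has an open endpoint window. A loss rate computed then is not the first-year rate that the Outcomes section defines. What it would miss is the later part of the year, including losses during oncological treatment, which the outcome expressly covers.

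This matters because the study is single-arm and the loss rate is its central estimate. The research hypothesis is that the procedure is safe, and the Sample size section treats 5% loss as acceptable. Incomplete follow-up counted as success would move the estimate towards that hypothesis. Dropping incomplete women would leave fewer than the precision calculation needs.

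**Working it through.** **1. The plan's own sample size.** Inputs from Sample size: loss rate p = 5%, precision d = 5 points, 95% confidence, 10% losses to follow-up.

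- n = 1.96² × 0.05 × 0.95 / 0.05² = 72.99, so 73 evaluable women.
- Allowing for 10% losses: 73 / 0.9 = 81.1, which matches the stated 81.
- The planned half-width therefore rests on about 73 women with the outcome observed.

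**2. The gap.** The window is 12 months (Outcomes) and the shortest follow-up at the report is 3 months (Trial results). Women included in the last 12 − 3 = 9 months of accrual are incomplete. With even accrual over A months (assumption), their share is f = 9/A.

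**3. Range for A (assumption).** The article gives two indirect anchors.

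- If the preliminary report at 2–3 years is the same as the report at 3 months after last inclusion, A = 24 − 3 to 36 − 3 = 21 to 33 months. The article does not say that they are the same report.
- If final data at 6–7 years means accrual plus 5 years of follow-up, A is about 12 to 24 months.

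Neither anchor leaves time for analysis and publication. Together they span 12 to 33 months.

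**4. Two illustrations of the effect.** The article does not say how incomplete women would be handled in this report.

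- *Counted as no loss.* Follow-up of incomplete women is spread evenly from 3 to 12 months, mean 7.5. With a constant hazard, and treating risk as proportional to time (reasonable at 5%), a true 5.0% reads as 5.0% × [1 − f × (1 − 7.5/12)].
- *Left out.* Remaining n = 81 × (1 − f), and the half-width is 1.96 × √(0.05 × 0.95 / n).

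| Accrual A (months) | Share under 12 months | Women, of 81 | Reading of a true 5.0% | Women left | Half-width (points) |
|---|---|---|---|---|---|
| 12 | 75% | 61 | 3.6% | 20 | 9.5 |
| 21 | 43% | 35 | 4.2% | 46 | 6.3 |
| 24 | 37.5% | 30 | 4.3% | 51 | 6.0 |
| 33 | 27% | 22 | 4.5% | 59 | 5.6 |

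The last two columns are before other losses, whereas the planned 73 is after them. Taking off 10% leaves about 42 women (6.6 points) at 21 months and 53 (5.9 points) at 33 months.

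If the report waits for the last woman's 12 months, f = 0. All 81 women, or about 73 after losses, then have the full window and the planned 5 points is recovered.

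**The case against.** Four arguments can be made for the plan.

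- **The main result may mean the whole main objective.** That objective covers postsurgical complications as well as implant loss. The complications with a stated window close by 3 months (bleeding 7 days, infection 30 days, skin necrosis 3 months), and Table 1 has a 3-month time point. This may explain the wording. It does not resolve the conflict: Outcomes makes complications secondary and implant loss the only primary outcome, and the main objective includes implant loss too.
- **Reporting is staged.** The early data are called preliminary and final data come at 6–7 years. Every woman is followed at 12–18 months and again at 5 years. This stands. A reader might infer that the 12-month outcome would never be obtained; the article does not support that. The problem is confined to a first report that is presented as sufficient for the main result.
- **Handling of incomplete women is not stated.** A reader might infer that they must be either counted as free of loss or dropped. The article says neither. The missing-data sentence does not say whether women still under follow-up count as missing. Restricting the report to women with 12 months, or censoring, is not ruled out, and such detail may sit in a plan that is not shown. The two effects above are therefore illustrations, not predictions.
- **The effects are modest.** Over 21 to 33 months of accrual the bias is under 1 point against a planned precision of 5, and precision worsens by about 0.6 to 1.3 points. This stands for that range. The effects grow if accrual is shorter, and the accrual length is not known.

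**Conclusion.** The point holds as an inconsistency in the current text: a first-year primary outcome cannot be fully assessed 3 months after the last inclusion, and nothing in the article reconciles the two statements. That conclusion needs no assumption about accrual.

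Its size does. With even accrual over 12 to 33 months, at least about a quarter of the women (27%), and up to 75%, would be reported before their window closes. The distortion of the estimate is small to moderate for accrual of 21 months or more and larger at 12 months. The bias figures also assume a constant hazard over the year and shrink if losses cluster early. Eligibility, endpoint definition, data collection and sample size are not affected.

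**What to change.** Change the sentence under Trial results so that the primary implant-loss analysis is run when the last included woman has completed 12 months after surgery or has had an earlier implant loss. If a report at 3 months is still wanted, label it interim and descriptive, covering early complications and 3-month implant loss, and do not call it the main result. Align the preliminary-data timing under Ethics and dissemination with whichever report is meant.

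The cost is a wording change and a main-result report about 9 months later (12 − 3). The sample size stays at 81 and no extra data are collected.
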